## Abstract

**Background:**

For patients with advanced cancer, visits to the emergency department (ED) are common. Such patients present to the ED with a specific profile of palliative care needs, including burdensome symptoms such as pain, dyspnea, or vomiting that cannot be controlled in other settings and a lack of well-defined goals of care. The goals of this study are: i) to test the feasibility of recruiting, enrolling, and randomizing patients with serious illness in the ED; and ii) to evaluate the impact of ED-initiated palliative care on health care utilization, quality of life, and survival.

**Methods/Design:**

This is a protocol for a single center parallel, two-arm randomized controlled trial in ED patients with metastatic solid tumors comparing ED-initiated palliative care referral to a control group receiving usual care. We plan to enroll 125 to 150 ED-advanced cancer patients at Mount Sinai Hospital in New York, USA, who meet the following criteria: i) pass a brief cognitive screen; ii) speak fluent English or Spanish; and iii) have never been seen by palliative care. We will use balanced block randomization in groups of 50 to assign patients to the intervention or control group after completion of a baseline questionnaire. All research staff performing assessment or analysis will be blinded to patient assignment. We will measure the impact of the palliative care intervention on the following outcomes: i) timing and rate of palliative care consultation; ii) quality of life and depression at 12 weeks, measured using the *FACT-G* and *PHQ-9*; iii) health care utilization; and iv) length of survival. The primary analysis will be based on intention-to-treat.

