## Methods

### Design

To evaluate the impact of ED-initiated palliative care consultation on quality of life, health care utilization, and survival on patients with advanced cancer, we are conducting a patient-level, single center, single blind pilot randomized controlled trial of 125 to 150 participants. The Institutional Review Board at the Icahn School of Medicine at Mount Sinai Hospital approved all study procedures (GCO 08–1234), and every participant provided informed consent.

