### Analysis

We estimated our sample size based on one of our primary outcomes (time to palliative care) by utilizing data from the palliative care database on consultation in patients with advanced cancer. The baseline mean time to consultation for such patients seen by palliative care was 9 days (SD = 12). We estimated that our intervention would decrease this number by at least 50%, to 4.5 days (estimated SD = 6 days). Calculations employ two-tailed tests (α = 0.05, with β = 0.80). We plan to enroll and randomize at least 140 patients. We expect to have at least 80% power with α = 0.05 (two-sided) to detect clinically meaningful differences in these primary outcome variables with 70 subjects/group.

The primary analysis will be a traditional intention-to-treat that will compare intervention to control subjects on our predetermined primary and secondary outcomes. Two sample *t*-tests, Mann–Whitney, or *χ*^2^ will be used as appropriate depending on whether the outcome is continuous or discrete, and whether it is normally distributed. For the quality of life data, where there is a baseline score, ANCOVA will be used to compare outcomes between the two groups, and patients who die will be excluded from this analysis. A series of secondary analyses will be conducted if there is significant contamination between the intervention and control group. In the first of these sets of analyses, randomization assignment will serve as an instrumental variable and percentage of admissions receiving palliative care will be included as a covariate. We will also compare primary and secondary outcomes per protocol (i.e., patients will be grouped according to whether they received a consultation, rather than on their randomization scheme). We expect outliers in our outcome data and will not be excluding them from the analysis. Because of the small sample size, we will not account for permuted blocked randomization in the analyses.

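### The planned enrolment of 125 to 150 contradicts the minimum of 140 behind the 80% power claim, and the same Analysis paragraph prints β = 0.80 where power is meant

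*Protocol article*

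**What the plan says.** The protocol article gives the size of the trial in three places.

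- Abstract, Methods/Design: "We plan to enroll 125 to 150 ED-advanced cancer patients".
- Methods, Design: a "single blind pilot randomized controlled trial of 125 to 150 participants".
- Methods, Analysis: "We plan to enroll and randomize at least 140 patients".

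The Analysis section bases the sample size on one of the primary outcomes, time to palliative care consultation. It assumes a mean of 9 days (SD 12) without the intervention and 4.5 days (SD 6) with it. The error rates are given as: "Calculations employ two-tailed tests (α = 0.05, with β = 0.80". Two sentences later comes the power claim: "We expect to have at least 80% power with α = 0.05 (two-sided") "to detect clinically meaningful differences in these primary outcome variables with 70 subjects/group".

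**The concern.** A floor of 125 and a floor of 140 cannot both hold. The figure of 140 lies inside the range 125 to 150, so the conflict concerns the lower part of that range: 125 to 139 patients is within plan according to the abstract and the Design section and below plan according to the Analysis section. All three statements are current text about patients to be enrolled, and the Analysis sentence adds randomisation. The gap is therefore not explained as enrolled versus evaluable patients, and no allowance for attrition is described.

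At stake is the meaning of the power claim and the point at which recruitment is complete. If the trial closed at 125, it would have met its size as published in two places while falling short of the size on which its stated power rests. A reader who takes the size from the abstract and the power from the Analysis section would credit the trial with 80% power that it does not have on its own assumptions.

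Separately, β conventionally denotes the type II error rate. Printing it as 0.80 states 20% power in the same paragraph that claims at least 80%.

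**Working it through.** **Inputs**

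- Means 9 and 4.5 days, so the difference is δ = 4.5 (Analysis).
- SDs 12 and 6, so the sum of variances is 144 + 36 = 180 (Analysis).
- Two-sided α = 0.05, z = 1.96; power 80%, z = 0.842 (Analysis).
- Equal allocation, taken from the balanced blocks in Randomization and blinding.

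**Step 1. Reproduce the plan's figure.** With the normal approximation,

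n per group = (1.96 + 0.842)² × (12² + 6²) / 4.5² = 7.85 × 180 / 20.25 = 69.8, rounded up to 70.

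That is 140 in total, exactly the Analysis figure. Other readings of the inputs do not return 70: SD 12 in both groups gives 112 per group, SD 6 in both gives 28, a simple average SD of 9 gives 63, and a one-sided test gives 55. So 140 is the derived number, and it comes from 80% power.

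**Step 2. Power across the stated range.** Power = Φ(δ / SE − 1.96), with SE = √(180 / n per group).

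| Total | n per group | SE | δ / SE | Power, normal | Power, Welch t |
|---|---|---|---|---|---|
| 125 | 62.5 | √2.880 = 1.697 | 2.652 | 75.5% | 74.6% |
| 140 | 70 | √2.571 = 1.604 | 2.806 | 80.1% | 79.4% |
| 150 | 75 | √2.400 = 1.549 | 2.905 | 82.8% | 82.1% |

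With whole patients at 125, the Welch figure is 74.4% or 74.9%, depending on which group has 62 and which 63. For 80% power by Welch t, 72 per group (144 in total) are needed.

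**Step 3. β read literally.** β = 0.80 means power 0.20, z = −0.842:

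n per group = (1.96 − 0.842)² × 180 / 20.25 = 1.25 × 8.89 = 11.1, rounded up to 12.

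The plan's 70 per group is therefore incompatible with β = 0.80 and matches β = 0.20.

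**The case against.** The strongest reply has four parts.

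- **The power claim is conditional.** It is tied expressly to 70 per group, and the ranges in the abstract and Design section describe planned size; they are not stopping rules. Reporting 80% power at 125 would contradict the Analysis section itself. This is fair and limits the harm: the article does not claim 80% power at 125. It does still declare two different minimum sizes.
- **The trial is a pilot.** Feasibility is its first goal, its effect estimates are meant to inform a larger trial, and no decision in the article turns on 75% versus 80%. This stands as a reason to call the point modest. But a protocol that makes an explicit power claim on a primary outcome should make it consistently.
- **The β slip has no consequence.** That is correct. The 70 per group follows from 80% power, and the true meaning is plain two sentences later. It is an error of notation only.
- **The power figures are themselves optimistic.** The inputs describe patients who were seen by palliative care, whereas under Usual care a consultation takes place only if a clinician requests it. Days to consultation may therefore be missing for some randomised patients, and power computed on the number randomised assumes a value for everyone. This caveat stands, but it applies equally to the plan's 80% and does not reconcile the two enrolment targets.

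An average SD of 9 would give 126 in total and 79.8% power at 125, which might explain the lower bound. The article does not say that this was used, and it does not return the stated 70 per group.

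**Conclusion.** The concern holds. The article states two incompatible minimum sizes, and only the larger delivers the stated power on the plan's own inputs. At 125 patients power is about 75%, so the chance of missing the assumed effect rises from about 20% to about 25%. The figure of β is wrong as printed, without numerical consequence.

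These figures assume the plan's means and SDs, a comparison of means, a near-equal split, and an observed consultation time for every randomised patient. The split is not guaranteed at 125, because blocks of 50 leave the third block half filled. At the extremes, Welch power would be 78.4% with 75 patients in usual care and 50 in the intervention, and 67.7% the other way round; both are still below 80%.

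**What to change.** State one enrolment target in the abstract, the Design section and the Analysis section. Either:

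- make 140 the minimum in all three, noting that the 80% rests on the normal approximation (80.1%; Welch t gives 79.4% and would need 144); or
- keep 125 to 150 in all three, remove the minimum of 140, and give power as a range of about 75% to 82% (Welch t 74.6% to 82.1%; normal 75.5% to 82.8%), with the note that it assumes a consultation time for every randomised patient.

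Replace the printed β with β = 0.20 (power 0.80).

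The edits are to wording only. Under the second option the stated power becomes slightly less favourable; under the first, the trial commits to up to 15 patients more than its present lower bound (140 − 125).

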**Discussion:**

This pilot randomized controlled trial will test the feasibility of recruiting, enrolling, and randomizing patients with advanced cancer in the ED, and provide a preliminary estimate of the impact of palliative care referral on health care utilization, quality of life, and survival.

**Trial registration:**

Clinical Trials.gov identifier: NCT01358110 (Entered 5/19/2011).

## Background

Palliative care utilizes an interdisciplinary, collaborative, team-based approach to decrease pain and suffering for patients with advanced illness. The goal is to achieve the best possible quality of life, including physical, psychological, social, and spiritual aspects, for patients and families through specific knowledge and skills [1]. Palliative care, as distinct from hospice, is not limited to end-of-life care and is offered simultaneously with life prolonging therapies for persons living with serious chronic illness. It has been shown to significantly improve patient and family member quality of life, while at the same time reducing healthcare costs, improving patient and caregiver satisfaction, reducing distressing symptoms, such as pain or dyspnea, improving quality of care, and reducing hospital length-of-stay and costs per day, thereby reducing overall healthcare expenditures [2-4].

Bringing palliative care into the emergency department (ED), a place designed more to intervene than to comfort, is an important place to begin to make improvements in this area. In addition, offering palliative care services from the ED, at the beginning of the hospital course, might provide even greater benefit to patients, families, and hospitals than inpatient consultation, which often occurs late in a patient’s hospital course [5]. As of 2008, palliative care is an official sub-specialty of Emergency Medicine.

This is a protocol for a single center, parallel, two-arm randomized controlled trial in ED patients with metastatic solid tumors comparing ED-initiated palliative care referral to a control group receiving usual care. We chose not to use a pain management team, social worker, or other supportive care intervention as an attention control as we are interested in whether early comprehensive palliative care consultation impacts quality of life, health care utilization, and survival, not whether this is due to the supportive care aspect of palliative care teams alone. We also made this decision to make the intervention more easily generalizable.

The goals of this study are: i) to test the feasibility of recruiting, enrolling, and randomizing patients with serious illness in the ED and ii) to evaluate the impact of ED-initiated palliative care on health care utilization, quality of life, and survival. To decrease bias in the measurement of baseline and outcome data, all study staff that perform patient follow-up, chart abstraction, or data analyses are blinded to patient assignment. We will measure the impact of the palliative care intervention on the following outcomes: i) timing and rate of palliative care consultation; ii) quality of life and depression at 12 weeks, measured using the *FACT-G* and *PHQ-9*; iii) health care utilization; and iv) length of survival.

## Methods

### Design

To evaluate the impact of ED-initiated palliative care consultation on quality of life, health care utilization, and survival on patients with advanced cancer, we are conducting a patient-level, single center, single blind pilot randomized controlled trial of 125 to 150 participants. The Institutional Review Board at the Icahn School of Medicine at Mount Sinai Hospital approved all study procedures (GCO 08–1234), and every participant provided informed consent.

### Setting

Mount Sinai Hospital is a quaternary care, academic referral center in New York City and its ED is an active, urban emergency department. Annually, approximately 100,000 patient visits are seen in the ED’s Adult and Pediatrics divisions. The ED provides patient care 24 hours per day, seven days per week, to all who seek care. The trial will be conducted in the flow of routine patient care.

### Participants

#### Inclusion criteria

Research coordinators screen the electronic medical record ED track board for patients with our specific advanced cancer staging criteria (Table 1) 8 to 12 hours a day, Monday through Friday. The ED attending on record and the patient’s medical oncologist have to agree before research staff invite the patient to participate. Patients eligible for participation are those with a known advanced cancer that meets our staging criteria who are able to speak English or Spanish fluently, and who are being admitted to or observed in the hospital.

**Table 1 T1:** Cancer staging criteria

**A**	**B**
**Cancer location**	**Cancer type**
Anal	“metastatic”, “mets to”, spread to, recurrent “unresectable”, “locally advanced”, “not a surgical candidate”, Stage IV, other
Brain	Recurrent, relapsed, not a surgical candidate, mets to, refusing surgery/radiation, chemotherapy, other
Breast	“metastatic”, “mets to”, “spread to”, Stage IV, other
Carcinoid	Unresectable, metastatic, mets to, refusing chemo/surgery, not a surgical candidate, Stage IV, other
Cervical	“metastatic”, “mets to”, spread to, recurrent “unresectable”, “not a surgical candidate,” Stage IV, other
Colon/Rectum/Colorectal	“metastatic”, “mets to”, spread to, recurrent “unresectable”, “locally advanced”, “not a surgical candidate”, Stage IV, Dukes D, other
Endometrial/Uterine	“metastatic”, “mets to”, spread to, recurrent “unresectable”, “not a surgical candidate”, Stage IV, other
Esophageal	“metastatic”, “mets to”, spread to, recurrent “unresectable”, “locally advanced”, “not a surgical candidate”, Stage III, Stage IV, other
Gallbladder/Bile duct/Cholangio/Ampullary	“metastatic”, “mets to”, spread to, recurrent “unresectable”, “locally advanced”, “not a surgical candidate”, Stage II, Stage III, Stage IV, other
Kidney/Renal cell	“metastatic”, “mets to”, spread to, recurrent “unresectable”, “not a surgical candidate”, Stage IV, other
Laryngeal/Throat/Nasopharyngeal/Mouth a.k.a Head and Neck	“metastatic to”, “locally advanced”, “spread to regional LN” “refusing surgery/chemo”, “not a surgical candidate”, recurrent, Stage III, Stage IV, other
Liver/Hepatic, Hepatocellular (HCC)	“metastatic”, “mets to”, spread to, recurrent “unresectable”, “locally advanced”, “not a surgical candidate”, “ineligible/not a transplant candidate”, ascites, Stage III, Stage IV, other
Lung or Non-small cell lung cancer (NSCLC)	“unresectable”, “metastatic”, “mets to”, “refusing surgery/chemo” “not a surgical candidate,” Stage IIIb, Stabe IV, recurrent, other
Lung small cell	“metastatic”, “mets to”, “refusing chemo”, recurrent, Extensive Stage, other
Melanoma	“metastatic”, “mets to”, spread to, recurrent, Stage IV, other
Mesothelioma	“unresectable”, “metastatic”, “mets to”, “refusing surgery/chemo,” “not a surgical candidate,” Stage III, Stage IV, recurrent, other
Multiple myeloma	Not a transplant candidate, relapse after transplant, Stage III, Stage IV, other
Osteosarcoma	Unresectable, metastatic, mets to, refusing chemo/surgery, not a surgical candidate, Stage IV, other
Ovarian	“metastatic”, “mets to”, spread to, recurrent “unresectable”, “not a surgical candidate”, Stage III, Stage IV, other
Pancreatic	“metastatic”, “mets to”, spread to, recurrent “unresectable”, “locally advanced”, “not a surgical candidate”, Stage III, Stage IV, other
Penis	Unresectable, metastatic, mets to, refusing chemo/surgery, not a surgical candidate, Stage IV, other
Prostate	“metastatic”, “mets to”, spread to, recurrent, Stage IV, other
Sarcoma	Unresectable, metastatic, mets to, refusing chemo/surgery, not a surgical candidate, not a transplant candidate, relapse after transplant, Stage IV, other
Stomach/Gastric	“metastatic”, “mets to”, spread to, recurrent “unresectable”, “locally advanced”, “not a surgical candidate” (exception for stage II gastric CA, not a surgical candidate is ELIGIBLE), Stage III, Stage IV, other
Thyroid (eligible papillary, follicular, medullary and all anaplastic)	Unresectable, metastatic, mets to, refusing chemo/surgery, not a surgical candidate, Stage IV, other
Vulva	Unresectable, metastatic, mets to, refusing chemo/surgery, not a surgical candidate, Stage IV, other
Other Confirm eligibility with Principal Investigator	“metastatic”, “mets to”, spread to, recurrent “unresectable”, “locally advanced”, “spread to regional lymph node,” “not a surgical candidate”, not a chemo candidate, not a transplant candidate, not a radiation candidate, relapsed, other

#### Exclusion criteria

Patients are excluded if they are unable to answer questions because of severe pain or lethargy, cancer stage is unclear, if they have been seen by palliative care in the past, or if they have evidence of cognitive impairment on the six-item screener [6]. Patients who are planning to leave the immediate geographic area (i.e., move to another state or country) are also excluded.

#### Recruitment

The study was described to ED attendings via email and during grand rounds before patient recruitment began, and staff were informed in real time once recruitment of one of their patients qualified for the study. Oncologists were similarly told about the study before patient recruitment began in person at their faculty meeting, as well as by email. A list of all oncologists with admitting privileges was made, and is continually updated specifying whether the oncologist prefers to be called in advance for every patient. If research staff identify a potential qualifying ED patient based on chart review, s/he discusses the patient with the ED attending and oncologist (if the oncologist requests this). If both agree to allow research staff to approach the patient, the patient is then interviewed at the bedside to ascertain whether they qualify for the study. If the patient meets inclusion criteria, informed consent is obtained in the ED, and patients are offered a $20 gift card as an incentive to participate. Multiple forms of contact (home and mobile numbers, friends and family numbers, and address) are collected to minimize loss of patients to follow-up.

### Interventions

#### Randomization and blinding

After the baseline survey is completed, the research assistant then relays the patient information to a separate research staff member (the “randomizer”) with no role in study recruitment, follow-up, or analysis (see Figure 1 for randomization scheme). Patients are randomized via pre-specified balanced block randomization in blocks of 50. If the patient is assigned to the treatment group, the “randomizer” then pages the palliative care consultation team to relay information about the patient (name, medical record number, ED attending and oncologist of record) and the reason for consultation. If assigned to the care-as-usual group, no further action is necessary. The list linking patient name and group assignment is stored on a secure network computer under password-protection, and accessible only to the “randomizer”. All research staff involved in recruitment and follow-up are blind to patient assignment. It is not feasible to blind patients or care providers to patient assignment.

**Figure 1 F1:**
[figure not shown]
Randomization scheme and participant flow diagram.

#### Intervention arm

If the patient is assigned to the intervention arm, the palliative care team is consulted within a few hours. Intervention patients receive a comprehensive palliative care consultation by the inpatient team the same or the following day. At Mount Sinai Hospital, inpatient comprehensive palliative care consultation consists of three components: i) symptom assessment and treatment; ii) establishment of goals of care and advance care plans; and iii) transition planning. The palliative care team is composed of a medical doctor, a nurse practitioner, a social worker, and a chaplain. The team uses validated symptom assessments and makes recommendations for symptom management using National Comprehensive Cancer Network guidelines [7]. They communicate these recommendations to consulting physicians (in this case, the oncologist) using standardized palliative care team chart notes and in person or by telephone. The palliative care team meets with patients, families, and care teams to identify goals of care, complete advance directives, and communicate difficult news (if requested) using standardized communication protocols. If admitted, the team sees patients daily to monitor implementation and results of treatment recommendations and to assess for new and ongoing symptoms. Reassessment and treatment modifications occur as needed to achieve goals of care. The palliative care team conducts or assists with discussions about new or changing goals of care, communicating bad news, and associated treatment adjustments. The team also works with the patients’ social workers and family to facilitate transition management consistent with goals of care. If the team finds ongoing palliative care needs that are expected to continue after discharge, they refer them to the outpatient palliative care clinic.

